###### Confounding variables/effect modifiers

3.4.2.3.3

We will collect information for a wide range of covariates identified from a detailed literature review. We will collect information using questionnaires and case report forms developed for this study. Wherever possible, relevant questions will be adapted from pre-existing validated questionnaires. To minimize attrition over time, we will ensure that an optimal number of questions will be asked without missing out on important information.

Child-specific details will be retrieved from discussions with care providers and by consulting available hospital records. Briefly, we will record information such as age, gender, birth order, status of immunization [i.e., as per the National Immunization Schedule (NIS) of the Universal Immunization Programme (UIP) in India (76)], history of anaemia and other acute morbidities (defined as per the Integrated Disease Surveillance Project (IDSP) (77) of the Government of India), relevant medical history, including at-birth details of APGAR score, length, weight, head circumference, mid-arm circumference, neonatal intensive care unit (NICU) admission, co-morbidities and family history.

We will collect family-specific information in the form of a household roster detailing the age, education, occupation, relevant medical history, and tobacco/alcohol consumption [using standard questions provided by the WHO STEPwise instrument (78)] of family members. Then, the household socioeconomic status (SES) will be categorized based on scores assigned using the latest revision of the Kuppuswamy Scale (79). Household water sanitation and hygiene assessment will be done using a pre-tested structured questionnaire which the study team has developed by adapting questions from the “Core questions on drinking-water and sanitation for household surveys” given by WHO/UNICEF (80).

In addition to the data collected at baseline, current pregnancy-related information will also be collected from the pregnant women. After birth, during monthly follow-ups with the child, the mother will be asked about breastfeeding and complementary feeding (after the child attains 6 months of age) practices. For data collection on complementary feeding, we will use relevant questions from a questionnaire previously used in Indian settings (81).

Finally, information about other environmental factors, such as the built environment and other indoor exposures, will be collected by adapting questions about built environmental factors such as ventilation, building material, area and construction of the house, and fuels used for cooking or heating from the ‘household questionnaire’ of the National Family Health Survey, India 2019–20 (NFHS – 5) and the ‘house-listing and housing census schedule’ of census 2011 (82, 83). Additionally, we will leverage the field experience gained by the study team in designing and using an exposure questionnaire in a previous cohort study conducted in central India, focussing on the impact of the built environment on population health (84–86).

### Data management

3.5

We will formulate a Data Collection and Management Committee (DCMC) consisting of the team’s principal investigator and other senior investigators. This committee will ensure that during the implementation of this research, the national guidelines for biomedical research data collection and management (87), are followed stringently to maintain the quality of data collection and analysis. For example, equipment used in the study will be routinely calibrated, and laboratory testing will be conducted using high-quality reagents. Research staff will be adequately trained before the start of project work. We will validate the study questionnaires, which have been developed by adapting questions from standardized tools, and these will be pilot-tested before use. DCMC will also handle requisite communication with the ethics committee and other ethical considerations, including data dissemination. The DCMC will ensure proper management of data. Filled questionnaires will be stored in secure locked cabinets, while online or computer-based information will be kept safe using passwords accessible only to the research team. All data forms will have a unique identifier, which will be used to link collected information on exposures, outcomes, and confounders to ensure accurate data integration while maintaining participant confidentiality. Data entry done by research staff will be supervised by the DCMC, who will randomly verify the entered data to check for data entry mistakes. We will use multiple imputation methods to manage missing data.

### Statistical analysis and reporting

3.6

The data will be entered using open access online applications from which the data will be downloaded and exported to SPSS statistics software (Version 25) and the latest versions of R packages/R studio for analysis. Data will be summarized using descriptive statistics like mean/standard deviation (SD) or median/Interquartile range. For categorical variables, summary estimates will be reported using frequency with percentages and within two selected study settings. An initial analysis will compare aggregated data between cities with high and low pollution levels. For this, relative risk (RR) and attributable risk (AR) will be calculated through the relevant equations using the probability of outcome (incidence/proportion) among the high pollution group (exposed) divided by the probability of outcome among the low air pollution group (relatively unexposed).

The next level of analysis will be based on the range of the estimates of PM_2.5_ /PM_10_ exposure concentrations and blood heavy metal levels found in the study participants (i.e., pregnant women/live-born children). We will use relevant correlation coefficients to assess possible correlations between environmental variables- PM2.5 /PM10/blood heavy metal levels and the health outcomes – growth indicator related z scores/development quotient/ARI episodes (Pearson or Spearman).

Finally, multivariable logistic regression model analyses will be used to study the relationship between environmental variables- PM_2.5_ /PM_10_/blood heavy metal levels and the health outcomes in binary forms – growth/development/ARI. Briefly, multiple linear mixed-effects regression model analyses will be used to study the relationship between the levels of early-life exposure (concentration of environmental pollutants- PM_2.5_ /PM_10_ concentration/ heavy metals in pregnant women and the child participant- monthly means for the former and cumulative mean- i.e., in-utero maternal exposure summed with infancy period exposure to heavy metal) and child health outcomes- mean anthropometric data (height, weight, head, and mid-arm circumference) and developmental level (obtained from developmental quotient/mean score on ASQ-3 scale) of each participant (live-born children) while adjusting for confounders. Similar regression equations will be used to analyze the association between exposure and delay in achieving growth and developmental milestones. Subsequently, the PM_2.5_, PM_10_ data and other environmental/sociodemographic data will be used in a logistic regression model of ARI symptoms within a distributed lag nonlinear modeling framework (DLNM) (88, 89). This approach will test the associations of PM_2.5_ /PM_10_ exposure over the preceding time periods and the distribution of growth z-scores / occurrences of ARI events (90–92).

Analyses will be performed separately for each child’s morbidity outcomes, such as growth/developmental parameters/domain. All analyses will adjust for different confounding variables included in the study. Details of such confounders for statistical adjustment will consist of gender, family size, socioeconomic status, gynecological/obstetrics/other relevant medical history, and data from environmental assessments of the households (built environmental attributes). We will also adjust for the effect of low birth weight and small-for-gestational-age on the studied association (Supplementary material). We will also conduct sensitivity analyses to test the robustness of our findings, for example, analysing a subset with complete data and comparing the results with the entire dataset where missing data imputations have been done.

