#### Sample size calculation

3.3.1

The calculated sample size is 571 mother–child pairs. Our main objective is to investigate the effect of early-life exposure to air pollution on child growth/development. Stunting, a prevalent manifestation of chronic malnutrition, is one of the significant indicators for delay in the achievement of growth/developmental milestones in children (47). Hence, we have calculated the sample size by assuming a power of 80%, a two-sided confidence level of 95%, and by using data available from a recent publication (48). This article estimated an odds ratio (OR) of 1.74 for stunting among under-five children with long-term exposure to PM_2.5_. We applied relevant continuity correction and inflation to account for participant exclusions during follow-up and anticipated non-response/participant attrition. Thus, we will enroll 783 pregnant women in each study city (1,566 participants in total) to establish the final cohort of 571 mother–child pairs. Further details of sample size calculation have been enumerated in Supplementary material (Data Sheet 2). We will continue to use the same cohort for our subsequent objectives.

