#### Sampling strategy

3.3.2

We will obtain information about eligible pregnant women in the study area from community health workers (CHWs), who are usually the first point of contact for antenatal care (ANC) among Indian pregnant women (49, 50). Before the launch of the study, we will identify and enlist, with the help of relevant district-level offices, all the CHWs working in both study cities under the Integrated Child Development Scheme (ICDS) and National Health Mission (NHM) (51, 52). These include Anganwadi workers (AWW) and Accredited Social Health Activists (ASHA), respectively (49, 50). We will approach all CHWs to gain their consent to cooperate, and those willing will be briefed about the study participant enrollment procedure.

We will contact pregnant women identified by CHWs at their homes or at the nearest Anganwadi Centre [community maternal and child care centre in India functioning under the ICDS (53)] to describe our study, confirm their eligibility using a pre-designed checklist, and finally obtain written informed consent. After administration of written informed consent (including consent for follow-up of their child for one year), pregnant women will be enrolled for participation in the study.

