#### Exposure data collection

3.4.1

A multi-pronged strategy will be used to collect individual and neighborhood-level exposure data. To begin with, historical data on the neighborhood-level concentration of air PM (PM_10_ and PM_2.5_) covering the two study cities will be retrieved from available open-access sources. For example, in India, in addition to using satellite-derived aerosol optical depth as a source for PM data, the Central Pollution Control Board (CPCB) provides freely available information from its network of fixed-site automatic monitors (continuous ambient air quality monitoring stations - CAAQMS) and gravimetric samplers under the National Air Quality Monitoring Program (NAMP) (54, 55). Using the city-level air PM data, we will develop an exposure database at a high spatial scale using the Land Use Regression (LUR) model for both cities. LUR has been widely used to predict the concentration of air pollutants (measured through distant fixed site monitors and/or remote sensing data) at target locations (i.e., the residential addresses of the selected participants) (56–58). We will develop our LUR model to assign ambient PM_2.5_ and PM_10_ exposure to each participant based on the geocodes of their residence. We will follow the methodologies previously published for urban area LUR models, such as that under the ESCAPE project (59) and for Indian cities (60, 61). Accordingly, in our LUR model, we will use data for a range of geographic, population, and emission source-specific predictor variables retrieved from open access sources, including satellite data, local authorities, and/or collected from field-level verification. For example, data on land use, road network, population density, elevation, meteorological, and other relevant variables will be used, in line with previous studies (56–58). We will adopt a supervised forward addition linear regression approach for model development and perform diagnostics on the fitted models to maintain the linear regression. Finally, we will assess the performance of the developed model by adopting a 10-fold cross-validation approach (62). In addition, we will also measure the personal exposure to air PM (PM_10_ and PM_2.5_) of each enrolled pregnant woman once in each trimester after enrolment to increase the accuracy of PM exposure data while accounting for participant mobility. For these measurements, low-cost battery-operated portable sensors will be used, as has been reported in previous studies (63, 64).

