We have attempted to overcome this limitation by incorporating past exposure open-access data (such as CPCB ground monitoring stations/satellite-based estimates) of PM_2.5_ into our constructed LUR models. Previous studies have used this method. For example, the recently published Californian population-based prospective pregnancy cohort study (MADRES) enrolled pregnant women with a gestational age of less than 30 weeks and obtained air pollution exposure information using data from the United States Environmental Protection Agency Air Quality System to model daily participant exposure beginning from 2 years before pregnancy (130). However, using only LUR modeling-based exposure assessment suffers from ecological fallacy (131). Final estimation is highly dependent upon the density of monitoring stations from which PM data can be used to train the models and the granularity of data for predictor variables and, thus, cannot accurately differentiate between individual-specific exposure, particularly when their residential addresses are clustered close together (132, 133). Hence, data triangulation by adding personally measured and biomonitoring data would increase confidence in the overall exposure assessment (134). We have thus adopted a multi-pronged strategy to estimate the study participants’ accurate exposure information.

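### The binary-outcome logistic models name no locality term or cluster-robust variance, so standard errors for residence-based PM will be too small if neighbours share residual risk

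*Protocol article*

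**What the plan says.** **Model.** Section 3.6 assigns multivariable logistic regression to the outcomes in binary form: "multivariable logistic regression model analyses will be used to study the relationship between environmental variables" (PM2.5, PM10, blood metals) and growth, development and ARI. The next sentence assigns linear mixed-effects models to anthropometry and developmental level, without naming a grouping level. A further sentence says that similar equations will be used for delay in reaching milestones. ARI symptoms also get a logistic model within a distributed-lag framework. The adjustment list covers child, family, medical and household items, and has no city or area term.

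**Recruitment.** Section 3.3.2: "We will obtain information about eligible pregnant women in the study area from community health workers (CHWs". The Discussion adds that these workers usually live in the locality they serve.

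**Exposure.** Section 3.4.1 uses LUR to assign ambient PM "exposure to each participant based on the geocodes of their residence", and section 3.4.2.3.1 defines the PM variable at each participant's location. The Discussion says that LUR used alone "cannot accurately differentiate between individual-specific exposure, particularly when their residential addresses are clustered close together". Section 3.4.1 also plans personal PM measurement once per trimester after enrolment.

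**Sizing.** The study is sized on stunting, a binary outcome (section 3.3.1 and Table 1).

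**The concern.** The standard error from a logistic model without a cluster term is valid if children are independent given the covariates. Two features of this design work against that. Location-based PM is largely common to neighbours. Neighbours may also share causes of stunting and infection that the covariates do not fully capture; about a quarter of each city's population lives in slums (26.68% and 23.32%, section 3.2), so locality differences in risk are plausible.

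When both the exposure and the residual risk cluster by locality, the effective amount of information about PM is smaller than the number of children suggests. Intervals for the PM odds ratios are then too narrow. A chance overlap of a more polluted locality with a higher-risk one can pass a nominal 5% test. The article intends its findings to support planning and policy, so the validity of these intervals matters.

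The point concerns dependence between different children in one locality. It does not concern repeated records of one child or the contrast between the two cities.

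**Working it through.** **Inputs from the protocol article.** Two-sided 5% level ("assuming a power of 80%, a two-sided confidence level of 95"%); sizing effect ("This article estimated an odds ratio (OR) of 1.74 for stunting among under-five children"); sample size ("The calculated sample size is 571 mother–child pairs"); 783 women enrolled per city.

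**Inputs assumed, because the article does not give them.** Latent-scale residual locality ICC 0.02, 0.05 and 0.10 (and 0 as a control); 5, 10 or 20 children per neighbourhood (m); baseline outcome risk 30%; 90% of PM variance between neighbourhoods.

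**The plan's own figure.** 571 can be neither confirmed nor refuted, because the baseline stunting proportion is in a supplement that is not shown. With OR 1.74, 80% power and a continuity correction, it is approached as a per-group figure at a baseline of about 8.5% (n = 568) and as a total at about 21% (n = 570). The check below was therefore run at N = 571 and at N = 2 × 571 = 1,142.

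**Step 1, formula.** The variance of the PM coefficient is inflated by about

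D = 1 + (m − 1) · ρx · ρy,

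where ρx is the between-neighbourhood share of PM variance and ρy is the outcome ICC on the observed (0/1) scale. The true size of the nominal 5% test is then 2 · [1 − Φ(1.96/√D)].

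A latent ICC corresponds to an intercept variance of ICC · (π²/3)/(1 − ICC). Integrating the logistic risk over that normal intercept at 30% baseline turns latent ICCs 0.02, 0.05 and 0.10 into ρy of about 0.014, 0.035 and 0.070.

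Example, latent ICC 0.05, m = 10, ρx = 0.9: D = 1 + 9 × 0.9 × 0.0347 = 1.28; 1.96/√1.28 = 1.73; true size 8.3%.

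**Step 2, simulation with no PM effect.** 2,000 datasets per setting, city term included, model-based logistic Wald test. Monte Carlo error is about ±1 percentage point near 5%, and somewhat more at the higher rates.

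| N | m | ICC 0 | 0.02 | 0.05 | 0.10 |
|---|---|---|---|---|---|
| 571 | 5 | 5.1% | 5.4% | 7.4% | 7.2% |
| 571 | 10 | 4.5% | 6.1% | 8.8% | 12.9% |
| 571 | 20 | 5.5% | 8.0% | 13.5% | 20.1% |
| 1,142 | 5 | 4.0% | 5.8% | 5.9% | 7.8% |
| 1,142 | 10 | 5.5% | 6.4% | 8.2% | 11.0% |
| 1,142 | 20 | 4.6% | 6.7% | 13.7% | 18.3% |

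At ICC 0 the test keeps its level (4-5.5%), so the excess comes from clustering. The pattern is much the same at either N, so the result does not depend on how 571 is read.

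**Step 3, how far the 90% share matters.** The formula at latent ICC 0.05:

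| ρx | m = 5 | m = 10 |
|---|---|---|
| 0.9 | 6.4-6.5% | 8.3% |
| 0.5 | 5.8% | 6.8% |
| 0.3 | 5.5% | 6.1% |

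**Step 4, does the remedy work?** In the same simulations a cluster-robust variance with a normal reference distribution rejected in about 4-8% with 57 or more neighbourhoods (highest 7.6%). With only 29 neighbourhoods it still rejected in about 9-10%, so a small-sample correction is needed there.

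**The case against.** **The article does not say that independence is assumed.** It names a model class and fixes no variance estimator, and a separate analysis plan could add a cluster term. This stands as a caution. However, the article names mixed effects in the very next sentence for other outcomes, and its adjustment list has no area item. Followed as written, the binary models have no protection.

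**The sentence on similar equations may extend mixed models to milestone delay.** Section 3.3.1 treats stunting as an indicator of such delay, so this reading is possible and stands. It does not settle the matter, because no grouping level is named, and a random effect for the child alone would not capture locality.

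**The LUR limitation is quoted in part.** The Discussion states it for LUR used alone and adds personal and biomonitoring data in response. That also stands: personal PM and blood metals vary more between neighbours and are affected less. The concern is with location-based PM.

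**The size is assumed.** This stands in full. Exposure windows differ between neighbours who are pregnant at different times, which lowers the between-neighbourhood share. Adjustment for socioeconomic status and household environment would absorb part of the ICC, and the simulation has no such covariates. All health workers in both cities are approached, so each may contribute few women.

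**A stronger reading that a reader might infer** is that the plan will produce false positives at several times the nominal rate, or that this is a sampled-cluster design. The documents support neither. They give no ICC, no catchment size and no PM variance split, and the dependence is by place and recruiter, not by sampling of clusters.

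**Conclusion.** The point holds for location-based PM. Section 3.6 names logistic regression for the binary outcomes with no locality term or cluster-robust variance, while the article itself describes exposure that neighbours largely share and recruitment through locally resident workers. The model-based standard errors of those PM odds ratios are too small whenever residual locality variation in risk remains.

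The size cannot be read from the documents. It is minor if localities contribute about 5 children each (about 5-8% at nominal 5%). It can be material with 10 (6-13%) or 20 (7-20%). These ranges assume latent ICC 0.02-0.10, about 30% prevalence and a 90% between-neighbourhood PM share, and all fall as that share or the residual ICC falls.

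A reader might also infer that the sample size is wrong for want of a design effect. The article mentions only that "We applied relevant continuity correction and inflation to account for participant exclusions during follow-up and anticipated non-response/participant attrition", but the full calculation is in a supplement that is not shown, so no such conclusion is drawn here.

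This is a worthwhile and inexpensive improvement to the stated analysis. It does not demonstrate that the results will be invalid.

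**What to change.** In section 3.6, state that the binary-outcome PM models will be fitted with a random intercept for locality, or as GEE or logistic models with cluster-robust variance and a small-sample correction when localities are few.

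- Define locality from the residential coordinates collected at baseline (section 3.4.2.1). Use the health-worker catchment only if it is recorded; the article does not say that it is.
- Keep city as a fixed term.
- Add the same locality level to the linear mixed models, and say what the similar equations for milestone delay are.
- Report the locality ICC.

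The cost is a few lines of text and no new data if coordinates are used. Confidence intervals for the location-based PM odds ratios become somewhat wider.

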###### Monthly follow-up of the child till 1st year of age

3.4.2.2.2

All eligible live-born children will be followed up at their homes/nearest Anganwadi centre. To ensure timely and smooth data collection, follow-up visits will be scheduled in a manner that these visits coincide with routine house-to-house visits carried out by CHWs under different ongoing national programs [such as Home-based newborn care (HBNC) and Home-Based Care for Young Child Programme (HBYC) under NHM and “Poshan Abhiyan” (72), “Dastak Abhiyan” specific to MP (73)]. In each monthly follow-up visit, anthropometry, achievement of developmental milestones, and acute morbidity profile will be recorded. Additional information about at-birth APGAR score, weight, length, head, and mid-arm circumference will be collected in the 5th visit (child age 1 month). Blood samples for heavy metal analysis and the data on child immunization and feeding practices will be collected in the 17th visit (during the 12th month of the child’s age).

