###### Study outcomes

3.4.2.3.2

The primary study outcomes are related to childhood growth and development, as shown in Tables 1, 2. In addition, we will also estimate the incidence rate of ARIs (number of episodes of ARI during infancy/total number of children under follow-up). We modified the Integrated Management of Childhood Illness definition for ARI [given by WHO/UNICEF (74)] which has been used previously (75) to create an operational definition of ARI for this study. Modification was done by incorporating the signs and symptoms mentioned in the Integrated Management of Neonatal and Childhood Illness (IMNCI), Ministry of Health & Family Welfare, Government of India. Accordingly, ARI will be defined as cough or difficulty in breathing with or without any general danger signs, with or without any chest indrawing, stridor, and fast breathing. Depending upon the site of inflammation determined by the paediatrician based on clinical signs and symptoms, it will be classified as ARI of the upper respiratory tract and ARI of the lower respiratory tract. Further, depending upon the severity, ARI will be classified as per IMNCI guidelines into “No Pneumonia: cough or cold,” “Pneumonia,” and “Severe Pneumonia or Very Severe Disease.” Based on previous research, we will define each episode of ARI to last for two weeks (75). When a child who has had no symptoms for at least one week develops signs and symptoms of ARI, we will treat that as a new episode (75).

**Table 1 tab1:** Operational definitions, indicators, and measurement methods to be used for child growth-related outcome measures.

Outcome	Operational definition	Variable/indicator	Measurement method
Small for gestational age (SGA)	As per the WHO definition of SGA given by the 1995 WHO expert committee, infants having a birth weight for gestational age below the 10th percentile based on a sex-specific reference population (139, 140).	Proportion of children diagnosed as SGA at birth (proxy of in-utero growth of the child)	Based on hospital records-verified by study staff
Low birth weight (LBW)	Infants with a birth weight of less than 2,500 g, regardless of gestational age at the time of birth (141, 142).	The proportion of children diagnosed as LBW at birth (proxy of in-utero growth of the child)	Based on hospital records-verified by study staff

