Overweight/ obese	Children’s body mass index (BMI - calculated as weight in kilograms divided by height in metres squared) will be plotted on WHO BMI charts and those with a BMI above the 95th percentile will be classified as obese and overweight will indicate those children whose BMI falls between the 85th and 95th percentile (143, 144).	The proportion of overweight/obese (based on BMI for age) infants at the end of the first year of life.	Monthly measurement of height/length, weight, and calculation of BMI
Underweight, wasted and stunted	*Z*-scores for growth indicators (length/height-for-age, weight-for-age, weight-for-length/height, BMI-for-age) will be estimated by comparing each child’s height/length and weight with WHO growth standards as shown in the image below (which has been adapted from the WHO child growth standards: training course on child growth assessment) (145). Based on where their calculated z-scores lie with respect to the median value of the standard reference population, children will be categorized as: Underweight: ‘weight for age’ below minus two standard deviations (-2SD) Severely underweight: ‘weight for age’ below minus three standard deviations (-3SD) Stunted: ‘height/length for age’ below minus two standard deviations (-2SD) Severely Stunted: height/length for age’ below minus three standard deviations (-3SD) Wasted: ‘weight for height/length’ below minus two standard deviations (-2SD)	Proportion of children with abnormal Z-scores for afore-mentioned growth indicators (i.e., underweight, severely underweight, stunted, severely stunted, wasted and severely wasted) at the end of the first year of life.	*Z*-scores for growth indicators (length/height-for-age, weight-for-age, weight-for-length/height, BMI-for-age) obtained from comparison of each child’s height/length and weight with WHO growth standards

**Table 2 tab2:** Operational definitions, indicators, and measurement methods to be used for child development-related outcome measures.

Outcome	Operational definition	Variable/Indicator	Measurement method

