Development progress	The developmental level of the child will be assigned a score ASQ-3 (146, 147). ASQ-3 has been widely used in many countries as a field-based parent-completed screening tool to assess five developmental domains (148). It has also been previously used and validated in the Indian population (149, 150).	Domain-specific and mean score of ASQ-3 obtained monthly	Ages and stages questionnaires- third edition (ASQ-3) questionnaire (146, 147)
	Developmental Quotient (DQ) is calculated by dividing Developmental Age by Chronological Age and multiplying it by 100 (151, 152). Developmental Age (DA): Each child will be assigned a DA at each follow-up visit for each of the 5 developmental domains, i.e., gross motor, fine motor, adaptive/cognitive, language and personal-social developmental domains. Study staff under the supervision of a paediatrician will estimate DA according to the achievement of domain-specific developmental milestones. Chronological Age (CA): the actual age of the child calculated from his/her date of birth	Proportion of children with delayed achievement of development milestones at the end of the first year of life. Domain-specific monthly developmental level of each infant obtained through Development quotient calculation	Questionnaire developed by authors and pilot-tested in an ongoing built environmental child cohort (84)

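### The mixed models sum maternal metal and month-12 infant metal into one term: part of it is measured after the earlier monthly outcomes, and its slope identifies neither association

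*Protocol article*

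**What the plan says.** Section 3.6 describes linear mixed-effects models whose outcomes are "child health outcomes- mean anthropometric data (height, weight, head, and mid-arm circumference) and developmental level". Particulate matter enters these models as monthly means. Metals enter as a "cumulative mean- i.e., in-utero maternal exposure summed with infancy period exposure to heavy metal". The next sentence applies similar equations to delay in growth and developmental milestones.

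On infant sampling, Section 3.4.2.2.2 says: "Blood samples for heavy metal analysis and the data on child immunization and feeding practices will be collected in the 17th visit", and places that visit in month 12. The text describes no other infant draw. On outcomes, the same section says: "In each monthly follow-up visit, anthropometry, achievement of developmental milestones, and acute morbidity profile will be recorded". Table 2 adds "Domain-specific and mean score of ASQ-3 obtained monthly".

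Two groups of outcomes have other timings. The binary growth indicators in Table 1 are set at the end of the year, for example "The proportion of overweight/obese (based on BMI for age) infants at the end of the first year of life", and small for gestational age and low birth weight are determined at birth.

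The correlation and logistic analyses in Section 3.6 refer to blood metal levels in women and children and state no sum. The distributed lag model is described for particulate matter only.

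**The concern.** There are two separate problems.

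The first is time order. A level measured in month 12 stands on the exposure side of models for outcomes recorded in earlier months. Growth, feeding or illness in those months may influence it. If so, an association that runs from the outcome to the infant level would be reported as an effect of exposure.

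The second is identification, and it applies at every age. One slope on a sum forces the same effect per unit on the mother's blood and the infant's blood. The resulting number answers neither the question about the maternal level nor the question about the infant level. Objective 3 in Section 2 names both pregnant women and children, and the aims distinguish pre- and postnatal exposure.

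At stake is the metal coefficient in the mixed models, which are the only models described for the repeated growth and development measures.

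**Working it through.** **Figure to reproduce.** The plan gives no effect size, SD or power for the metal analysis. The 571 pairs in Section 3.3.1 rest on stunting and particulate matter and play no part here.

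**Timing.** With twelve monthly ages and the draw at month 12, eleven of twelve outcome visits come before it. By visit number, the article puts visit 5 at age 1 month and visit 17 in month 12. That makes 17 - 5 + 1 = 13 visits, of which twelve come before the draw. On either count, all monthly visits but the last precede the infant measurement. If the mean anthropometric outcome is an average over visits, most of its inputs still precede the draw.

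**What the slope on a sum estimates.** Let M be the maternal level, C the infant level, v_M and v_C their variances, c their covariance, and b_M and b_C their slopes. Regressing the outcome on S = M + C gives

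b_S = [b_M(v_M + c) + b_C(v_C + c)] / (v_M + v_C + 2c)

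The inputs below are assumptions, because the article gives none. First take a purely prenatal effect (b_M = -0.20, b_C = 0). The share of b_M that is kept is (v_M + c)/(v_M + v_C + 2c):

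| SDs | corr. 0 | corr. 0.3 | corr. 0.6 |
|---|---|---|---|
| equal | 50% | 50% | 50% |
| infant twice maternal | 1/5 = 20% | 1.6/6.2 = 26% | 2.2/7.4 = 30% |
| maternal twice infant | 4/5 = 80% | 4.6/6.2 = 74% | 5.2/7.4 = 70% |

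Other effects behave differently:
- Equal effects (-0.20 and -0.20) give -0.20, with no dilution.
- Opposite effects (-0.20 and +0.20) at equal SDs cancel to 0.
- Opposite effects with the infant SD twice the maternal SD and correlation 0 give (-0.20 × 1 + 0.20 × 4)/5 = +0.12, the reverse of the maternal sign.

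**If the earlier outcome affects the later infant level.** Assume Y = b_M·M + e and C = r·M + g·Y + √(1 - r²)·u, with M, e and u independent standard normal. Then

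b_S = [(1 + r)b_M + g·var(Y)] / var(M + C)

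- With b_M = -0.20, r = 0 and g = -0.3: var(Y) = 1.04, the numerator is -0.20 - 0.312 = -0.512, the denominator is 1 + 0.0936 + 0.12 + 1 = 2.2136, and b_S = -0.23. This is larger than the true -0.20.
- With no prenatal effect, r = 0 and g = -0.3: b_S = -0.3/2.09 = -0.14, although nothing prenatal is acting.
- Simulation with n = 400,000, r from 0 to 0.6 and g from -0.1 to -0.3 gave -0.13 to -0.23 in the first case and -0.03 to -0.14 in the second. The maternal level alone gave about -0.20 in the first case throughout.

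**Is separating the terms enough?** Not for earlier outcomes. With r = 0.6 and g = -0.2, a joint model gives the infant slope g/(g² + 1 - r²) = -0.2/0.68 = -0.294. The maternal slope is then -0.20 + 0.294 × (0.6 + 0.04) = -0.01, against a true -0.20. The time order has to be respected as well.

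**The case against.** The aims define early-life exposure as both pre- and postnatal, so a combined index has a stated rationale. Both levels are blood concentrations from the same laboratory method (Section 3.4.1), so adding them is not a mismatch of units. The plan also calls the term a mean. Averaging in place of summing would double every slope above and so change the halving numerically. All of this is fair, but an average is the same mixture with the same test, and the timing is unchanged.

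Several stronger readings are tempting, and the article does not support them:
- A reader might infer that every metal coefficient is affected. The sum is stated for the mixed models and, through similar equations, for milestone delay. It is not stated for the correlations or the logistic models, and acute respiratory infection is not an outcome of the summed model.
- A reader might infer that Objective 3 cannot be answered. The other analyses can use the maternal level, and the objective does not ask for an isolated prenatal effect.
- A reader might infer that the infant sample follows all outcomes. The year-end indicators are about concurrent with it.
- A reader might infer that reverse causation is present. The design leaves it open and does not show it. Feeding as a cause of the month-12 level would be confounding, and feeding data are collected.
- A reader might infer that the sum always dilutes. The calculations show that it need not.

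**Conclusion.** The point holds for the mixed models of anthropometry and developmental level and for the similar equations on milestone delay. For outcomes before month 12, the infant part of the metal term is measured after the outcome. For all outcomes, the slope identifies neither the prenatal nor the infant association.

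The direction and size of the error cannot be fixed from the article. The shares of 50%, 20-30% and 70-80% hold only for a purely prenatal effect under the assumed SDs and correlations; other inputs give inflation, cancellation or a spurious slope. The timing conclusion assumes that the month-12 draw is the only infant sample. The text describes no other, but Figure 1 is not shown. Confidence is high on the timing and on the non-identification, and low on any particular size. The change should be made before analysis. The particulate matter analyses are not affected.

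**What to change.** In Section 3.6, remove the summed metal term and state the following:

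- For birth outcomes and monthly outcomes before month 12, the antenatal maternal level alone is the metal exposure. No sum is stated for the birth outcomes, so there this is a clarification.
- For month-12 outcomes, a maternal-only model is reported. The infant level is reported as a separate term, labelled cross-sectional. Where both enter one model, the maternal-only slope still stands beside it, because the infant level may lie on the pathway or reflect earlier growth.
- The month-12 infant level may serve as a prior exposure for outcomes in the later annual follow-up.

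The cost is a change of wording and slightly more analysis, with no new samples or assays. What is lost is a single cumulative index.
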